### Statistical methods

Continuous variables will be reported as mean and standard deviation using Student’s t-test. Categorical variables will be reported as frequency count and percentage using Chi-square test/Fisher’s exact test. Univariate analysis will be done to select variables for an adjusted multivariable analysis. Statistical significance will be set at P < 0.05 criteria. We will adopt imputation to address missing data.

Using complete set data analysis, cases undergoing ACT will be compared their own historical outcomes as controls. ED utilizations will be compared using the paired sample t-test or Wilcoxon Signed Rank test, the post-intervention utilization of ARFAs undergoing ACT will be compared to the pre-intervention utilization.

To adjust for potential confounders, multivariable regression analysis will be undertaken. Interactions will be tested for variables that are clinically relevant and are statistically significant. Model adequacy will be assessed through coefficients of determination (R2) and by plotting error terms against predicted values. Presence of multicollinearity will be evaluated by variance inflation factor (VIF). Should complete set analysis show efficacy, we will proceed to analyze the data using an intention-to-treat analysis.

The incremental costs of delivering the intervention will be estimated and compared to any observed cost savings from reduce usage of ED services and other health services. All analyses will be performed using R 4.2.0 (www.r-project.org) and STATA version 17.0 (StataCorp. 2017. Stata Statistical Software: Release 17.0. College Station, TX: StataCorp LLC) software.

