#### Secondary outcomes: cost analysis & health outcomes

*Cost Analysis*: The secondary outcome will first focus on the cost implications of healthcare resource consumption by ARFAs. We will analyse the costs generated at participating hospitals but cannot incorporate costs incurred at non-participating community institutions. We will calculate the net cost savings by comparing the cost of ACT during the intervention period against the cost savings from decreased ED encounters in the 12 months post-intervention.*Health Outcomes*: We will measure ARFA outcomes using the Christo Inventory of Substance-misuse Services (CISS) score, a validated marker of alcohol dependence severity, and the UCLA 3-point Loneliness Scale, a quick method for assessing social isolation. Furthermore, we will use the Center for Epidemiologic Studies Depression Scale Revised (CESD-R-10) to measure depression. Comparisons will be drawn between pre-ACT and post-ACT scores after six months of treatment.

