A further complication arises from ACT itself, which may result in decreased visits and an inability to complete the intervention. A patient appropriately institutionalized through ACT may lead to a loss of contact due to lack of access. To overcome this obstacle, we plan to foster collaboration with participating institutions and community partners, educating them about our research and establishing protocols for continued patient engagement. This coordinated approach aims to ensure that access to participants is maintained even if they are transferred to institutional care.

Difficulty in data collection is another expected barrier. Patients’ decreased brain function, inability to concentrate, and possible mild intoxication may result in missing data. To address this challenge, we will implement a flexible data collection approach, allowing for information to be gathered during subsequent visits if initial attempts are unsuccessful. Furthermore, we will employ trained researchers adept at working with this specific population, thereby maximizing the chances of obtaining complete and accurate data.

Notwithstanding these challenges, the potential for the ACT model to significantly enhance ARFAs’ physical and psychosocial well-being cannot be understated. The possibility of cost-savings and improved resource allocation within the healthcare system presents a compelling argument for further exploration of this model. Our study, guided by a pragmatic design, and informed by clear strategies to navigate these challenges, aims to contribute valuable insights into the effective treatment and management of ARFAs. We believe that our thoughtful approach to these barriers, combined with the innovative nature of our study, will ultimately allow us to successfully complete this important research.

The findings from our study are expected to be instrumental in informing healthcare frameworks and policy-making. Our research will provide critical evidence on cost-effectiveness, improved resource utilization, and potential for overall cost savings for Singapore’s healthcare system. With rising healthcare costs and demands, these insights could be transformational in enhancing the efficiency of emergency healthcare services.

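### The article names imputation but leads with an undefined complete-set comparison, and missing CISS, UCLA and CESD-R-10 scores may depend on the score itself, so apparent improvement can be overstated

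*Protocol article*

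**What the plan says.** All references are to the protocol article.

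- **Statistical methods, first paragraph:** "We will adopt imputation to address missing data". No outcome, analysis or method is named.
- **Statistical methods, second paragraph:** "Using complete set data analysis, cases undergoing ACT will be compared their own historical outcomes as controls". Complete set is not defined.
- **Statistical methods, third paragraph:** "Should complete set analysis show efficacy, we will proceed to analyze the data using an intention-to-treat analysis".
- **Secondary outcomes:** for the three scales, "Comparisons will be drawn between pre-ACT and post-ACT scores after six months of treatment".
- **Discussion, limitations:** a high dropout rate is expected and put down to the recurrent nature of addiction. Separately, "decreased brain function, inability to concentrate, and possible mild intoxication may result in missing data", with later attempts planned, "allowing for information to be gathered during subsequent visits if initial attempts are unsuccessful". A further route of loss is "A patient appropriately institutionalized through ACT may lead to a loss of contact due to lack of access".
- **Who is analysed:** the Inclusion criteria keep patients who discontinue after at least three ACT visits. The section on the multidisciplinary team-based intervention keeps patients who opt out.

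**The concern.** Two analysts could follow this text and report different results. One could restrict the scale comparison to patients with both scores, another to patients who completed ACT, and a third could impute first and analyse everyone. The article does not say which is meant. The analysis that keeps everyone is run only if the restricted one is favourable.

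The choice matters because the stated causes of loss are close to what the scales measure. The article describes CISS as a marker of how severe alcohol dependence is. A patient who has relapsed, or is too impaired to answer, is likely to score worse than one who can answer. Leaving such patients out, or filling their gaps from the scores of those who answered, then gives too good a six-month mean. At stake is the secondary hypothesis that ACT improves health outcomes.

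**Working it through.** **What the plan's figures give.** The sample size concerns ED visits only. It reproduces as (23 × (1.960 + 0.842) / 12.06)² = 28.55, rounded up to 29, with 12.06 = 0.40 × 30.15. It does not bear on the scales, for which the article gives no effect, SD or missing-data rate. The only loss figure is 15% attrition, in Trial flow and sample size.

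**Assumptions throughout (none from the documents).** Scores are in SD units, a higher score is worse, the pre/post correlation is 0.5 and the true mean change is zero. A negative result is a false improvement.

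**Check 1: loss at follow-up only.** Suppose 30% are impaired at six months and score 0.8 SD worse. Scores are missing in 70% of these and in 10% of the others.

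- Missing overall: 0.30 × 0.70 + 0.70 × 0.10 = 28%.
- Impaired share among those observed: (0.30 × 0.30) / (0.30 × 0.30 + 0.70 × 0.90) = 0.09 / 0.72 = 0.125.
- Bias: 0.8 × (0.125 − 0.30) = **−0.14 SD**.

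Simulation gives −0.14 SD for complete cases and also for regression imputation from baseline. With 20% impaired and 0.5 SD worse the bias is −0.06 SD. With 40% impaired and 1.0 SD worse it is −0.22 SD.

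For scale, the SD of change is √(2 × (1 − 0.5)) = 1, so the standard error is 1/√93 = 0.104 SD for the 93 patients recruited by March 2023. With 28% missing, 0.72 × 93 ≈ 67 remain and it is 1/√67 = 0.122 SD.

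**Check 2: loss at baseline as well.** The chance of a missing score now rises with the score at that time point (logistic, slope 1 per SD). Imputation is by regression on the other score.

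| Missing at follow-up | Missing at baseline | Complete-case bias (SD) | Imputation bias (SD) |
|---|---|---|---|
| 30% | 0% | −0.12 | −0.19 |
| 30% | 5% | −0.10 | −0.16 |
| 30% | 10% | −0.08 | −0.13 |
| 30% | 20% | −0.04 | −0.06 |
| 30% | 30% | 0.00 | 0.00 |
| 15% | 40% | +0.10 | +0.16 |
| 0% | 30% | +0.13 | +0.20 |

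With loss at follow-up only and at the plan's 15%, the complete-case bias is −0.07 SD.

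**Check 3: other mechanisms, 30% lost at follow-up only.** If loss depends on the baseline score alone, complete-case bias is +0.13 SD and imputation is unbiased (0.00). If the patients lost are those doing better, the biases are +0.13 and +0.20 SD.

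**Check 4: does better imputation cure it?** Adding a correlated auxiliary variable to the baseline score still left −0.11 to −0.18 SD at 30% follow-up loss. In the first row of the table, imputed scores would have to be worsened by 0.19 / 0.30 ≈ 0.65 SD to remove the bias. A tipping-point analysis explores shifts of this kind.

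**The case against.** The strongest reply is that complete set is contrasted with intention-to-treat and so may mean patients who completed ACT. The three-visit minimum fits that reading. Imputation could then operate within that set, in the intention-to-treat analysis, or for covariates. This stands. A reader might infer that the two sentences are strictly incompatible, but the article does not show that. It shows that they are unreconciled.

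A reader might also infer that either rule must make the scales look improved. The documents do not support this. The sentence on impairment and intoxication says only that they may cause missing data, and names no time point. Recruitment is mainly opportunistic, during hospital visits, so baseline scores can be lost for the same reason. Loss through institutionalisation could act either way. Later attempts, trained researchers and continued outcome collection after discontinuation should reduce the loss.

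Some of the article's own statements do point towards more loss at follow-up. It expects high dropout from recurrent addiction, the Background says these patients default mostly within three months, and patients unable to consent are excluded. A missed baseline score also has more later visits at which it can be recovered. That makes the direction plausible and no more.

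Finally, a reader might infer that ED counts would be imputed. No section says so. They come mainly from electronic records, and impairment at interview does not affect them.

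The imputation model itself may properly sit in an analysis plan that is not shown. The point here is what the article does fix: an undefined lead analysis set, and an all-patient analysis that depends on its result.

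**Conclusion.** The point holds for the three secondary scales. As written, the plan rests the scale comparison on an undefined set that may be selected in a way related to the outcome, and it reaches the all-patient analysis only after a favourable result. If loss is concentrated at six months among worse patients, both complete-set analysis and ordinary imputation overstate improvement. Under the stated assumptions this is by 0.06 to 0.22 SD, comparable with the standard error of 0.10 to 0.12 SD. The bias is about zero if baseline loss matches follow-up loss, and it runs against ACT if baseline loss is larger or if better patients are lost. Every rate, severity and correlation behind these figures is assumed, so they show that the risk is material, not that it will occur. The primary outcome is unaffected by this mechanism. This is a worthwhile, inexpensive improvement, not a fatal flaw.

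**What to change.** For CISS, UCLA and CESD-R-10:

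1. State what complete set means (both scores present, or ACT completed) and which analyses use imputation.
2. Make the main analysis all enrolled patients, with multiple imputation using the pre-ACT score, the number of ACT visits attended and ED visits during treatment. Do not make it conditional on the complete-set result.
3. Report the complete-set result as a sensitivity analysis.
4. Record the reason whenever a score is not obtained, at baseline as well as at six months.
5. Add a delta-adjusted (tipping-point) analysis in which imputed post-ACT scores are worsened step by step, and report the shift at which the conclusion changes. Imputing a value no better than the pre-ACT score can be one scenario. It should not be the main analysis: it leans one way and fails where the pre-ACT score is the one missing. Unfavourable imputation can also overcorrect. Imputing baseline plus 1 SD gave +0.21 SD against ACT even when only worse patients were lost at follow-up.

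Item 5 gives the protection if missingness depends on the unseen score, since Check 4 shows that a richer imputation model alone does not.

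The cost is a few sentences of plan text, one field on the data form and slightly more analysis work. The estimated improvement may come out smaller and less precise.

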## Background

Globally, in 2016, alcohol consumption ranked as the seventh primary cause for both mortality and Disability-Adjusted Life Years (DALYs), attributing to 2.2% of deaths in women and 6.8% in men. Almost one-tenth of worldwide deaths among the age group 15–49 years can be ascribed to alcohol consumption [1].

Patients who frequently utilize emergency department (ED) services due to alcohol-related issues are referred to as alcohol-related frequent attenders (ARFAs) [2]. These patients, often characterized by chronic alcohol misuse, constitute a small fraction of the ED population but disproportionately consume substantial emergency medical resources, including emergency medical services (EMS), EDs, and inpatient services [3, 4].

ARFAs not only present with acute symptoms of alcohol intoxication but also the long-term effects of alcohol misuse such as withdrawal symptoms, gastrointestinal bleeding, and complications of liver cirrhosis. Given the time-sensitive nature of EDs and the competing priorities therein, physicians often struggle to provide sustainable and long-term interventions to curb alcohol misuse in these patients [5].

Despite recommended treatment regimens for addiction, ARFAs frequently default, particularly within the initial three months. Data has suggested that this group of patients have high drop-out rates when referred for treatment [6]. Instead, this patient group often reverts to utilizing the ED and EMS, resulting in unplanned hospital admissions due to alcohol-related complications.

The acute and chronic presentations of ARFAs pose significant challenges, requiring substantial resources for close monitoring to prevent falls, dealing with potential staff abuse, cleaning services, and handling prolonged stays in crowded departments [7, 8]. Moreover, chronic alcohol misuse often leads to high-risk conditions like variceal bleeding and liver failure, thus escalating morbidity and mortality rates [9].

While extensive research on interventions for ARFAs [10], predominantly Case Management (CM), has been conducted in Western countries [11–13], few have explored the impact of assertive community treatment (ACT): a patient-focused, community-based approach which emphasizes the delivery of comprehensive and personalized services to patients.Despite a rigorous evidence base for CM, it has demonstrated variable reductions in ED use by ARFAs [14]. 

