#### The multidisciplinary team-based ACT intervention

Historical patient data are collected from the electronic health record system. We implement a multidisciplinary, team-based ACT intervention, targeting medical, psychiatric/psychological, social and substance (MPSS) domains. The ACT teams follow a predefined schedule, with each engagement spanning approximately 60 min. Interactions include CM and collaboration with a social service agency (SSA). Patients who opt out of the intervention will still be considered in the analysis.

The ACT team will maintain active engagement with ARFAs on a schedule detailed (see S Table 1), with a typical interaction lasting 60 min.

Each visit is not rescheduled in the event of a patient’s absence; instead, the team will re-engage the patient via phone to plan for the succeeding visit as per schedule. Consistent with the core principles of ACT, ARFAs are assertively engaged in the community, receiving intensive, comprehensive, and supportive care with a harm reduction approach. This also incorporates CM and collaboration with a SSA.

A typical ACT visit is as outlined in Fig. 3. “Assertive” in ACT means ACT workers lean forward in terms of patient recruitment and retention. This involves visiting patients in various non-traditional settings including but not limited to hospital admissions, nursing homes and incarceration. If the patient is uncontactable for individual visits, the research worker will go around the vicinity to look for the patient. In the event that a patient falls out with the research worker, an option to switch the research worker is available, as it is a counselling-based intervention.

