#### Primary outcome: number of ED visits

The primary outcome is the number of ED visits by ARFAs, sourced primarily from the electronic records system of the participating hospitals. A comparative analysis will be conducted between the rates of ED visits pre-intervention (12 months) and post-intervention (12 months).

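### Primary ED-visit comparison: count or rate, test and observed-time denominator are left open, and univariate covariate screening does not address time-varying confounding

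*Protocol article*

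**What the plan says.** All references are to the protocol article.

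- **Outcome.** The section on the primary outcome states: "The primary outcome is the number of ED visits by ARFAs, sourced primarily from the electronic records system of the participating hospitals". The next sentence sets up a comparison "between the rates of ED visits pre-intervention (12 months) and post-intervention (12 months" each side. One sentence gives a count, the other a rate, and no denominator is defined.
- **Test.** Statistical methods: "ED utilizations will be compared using the paired sample t-test or Wilcoxon Signed Rank test". There is no rule for choosing between them.
- **Who is analysed.** The primary comparison uses a complete set, missing data are to be imputed by an unnamed method, and intention-to-treat follows only if the complete set shows efficacy. Screening and recruitment says outcome data go on being collected after discontinuation. The section on the multidisciplinary intervention keeps opt-outs in the analysis.
- **Adjusted analysis.** "Univariate analysis will be done to select variables for an adjusted multivariable analysis". Fit is then judged as follows: "Model adequacy will be assessed through coefficients of determination (R2"), together with a plot of residuals against predictions and variance inflation factors. The stated aim is to adjust for confounders.
- **Where patients may be.** The team may meet patients in settings "including but not limited to hospital admissions, nursing homes and incarceration". The Discussion adds: "A patient appropriately institutionalized through ACT may lead to a loss of contact due to lack of access".

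**The concern.** A before-and-after comparison of visit counts is fair only if both years give each patient the same opportunity to attend. The before-year cannot contain a death. The after-year can, and it can also contain prison or residential stays. Because visits are read from records, a shortened after-year need not show up as missing data. It can appear as a full record with a low count, and that error favours ACT.

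The adjusted model is offered as protection against confounding, but each patient is his or her own control. Characteristics that do not change between the two years cannot explain a change between them. Screening such characteristics by P value does not address what can differ between the years, such as calendar trend and observed time. The study-design text nevertheless attributes changes in outcome to ACT.

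**Working it through.** **1. Planned effect and sample size (Trial flow and sample size).** The inputs are a baseline mean of 30.15 visits a year (SD 23.47), a 40% decrease, a planning SD of 23, 80% power and alpha 0.05.

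- Effect: 0.40 × 30.15 = 12.06 visits.
- Taking 23 as the SD of the paired difference, two-sided: n = (23 × (1.960 + 0.842) / 12.06)² = 28.55, so 29. The plan's figure reproduces.
- Attrition of 15%: 29 × 1.15 = 33.35, so 34 as stated. Dividing by 0.85 gives 34.1, so 35. The difference is immaterial here.

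**2. Spurious fall if lost time is ignored.** Assume no treatment effect, a fraction f of patients leaving observation at a uniformly random point of the after-year, and loss unrelated to visit rate. A lost patient contributes on average half the year, so the mean after-count is 30.15 × (1 − f/2). The values of f are assumptions; the article gives none for lost record time.

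| f | fall, f/2 | visits, 30.15 × f/2 | share of 12.06 |
|---|---|---|---|
| 5% | 2.5% | 0.75 | 6% |
| 10% | 5% | 1.51 | 12.5% |
| 15% | 7.5% | 2.26 | 19% |
| 20% | 10% | 3.02 | 25% |

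The 15% row equals the plan's attrition figure numerically, but that figure is not a forecast of deaths or institutional stays.

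**3. Effect on the test.** Overdispersed paired counts were simulated with no true effect (mean 30.15, SD 23.47, SD of the difference about 23, 1,500 runs per cell), keeping lost patients with their raw counts. Rejection rates of the paired t-test at the 5% level were:

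| n | nobody lost | 15% lost |
|---|---|---|
| 29 (required) | 4.4% | 6.7% |
| 93 (recruited by March 2023) | 4.6% | 15.1% |
| 340 (Table 1 maxima, 136 + 102 + 68 + 34) | 4.3% | 42.6% |

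The Wilcoxon test behaves alike (7.0%, 16.1% and 47.2% at 15% lost). Dividing visits by time observed brings the apparent reduction back to between −0.8% and +0.3% over all cells, including 30% lost. Dropping the lost patients gives −1.9% to +0.1%, with rejection of 3.9% to 5.5%, but only because loss was simulated as unrelated to visit rate.

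**4. Open choice of test.** With nobody lost, declaring success if either test is significant rejects in 5.8% to 6.3% of these runs. A second null simulation (SD about 25, n from 29 to 93, 2,500 runs) gave 5.6% to 6.9%.

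**5. Overdispersion.** Variance over mean is 23.47² / 30.15 = 550.8 / 30.15 = 18.3. This is a between-patient figure. The paired t-test still holds its level when nobody is lost (step 3).

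**6. Adjusted model.** Write a patient's visits in a period as (patient level) + (effect of fixed traits) + (calendar effect) + (ACT effect if after) + error. The after-minus-before difference is then (ACT effect) + (change in calendar effect) + error. The patient level and fixed traits have gone, but the calendar change remains. Fixed traits can still modify the size of the change; they cannot confound it.

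**The case against.** The strongest reply is that the text does not prescribe raw counts. It speaks of rates over equal 12-month windows, and a paired test can be run on per-patient rates. It also names a complete-set analysis and imputation, so a patient with a cut-off year might be dropped or imputed. A reader might infer that under this plan death counts as benefit. The documents do not support that: the handling of lost time is undefined, not fixed that way.

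Nor does the article forecast deaths in this cohort. The phrase "thus escalating morbidity and mortality rates" is general background on alcohol misuse. Nursing homes and prisons are listed as places where contact continues. The loss of contact in the Discussion concerns access to participants, with a mitigation, whereas ED visits come from records that do not need contact. All this stands. It makes the bias conditional but does not remove it, because reliance on records is what lets a truncated year pass as complete.

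It is also fair that R² is not the only check, that a linear model is an inference from it, that the covariates are not listed, and that the adjusted analysis is supportive. A test-choice rule, a denominator and a covariate list may sit in a full protocol or SAP not shown, so their absence alone is no finding. What remains is stated text: a count in one sentence and a rate in the next, two alternative tests, and a screening step unsuited to the stated aim.

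**Conclusion.** The point holds in a conditional form. The primary comparison is described inconsistently as count and rate, with two possible tests and no stated denominator, in a setting where the after-year can be cut short without appearing missing. If affected patients stay in unadjusted, ED use appears to fall by about half the fraction lost: 2.5% to 10% for 5% to 20% lost. False-positive risk then grows with sample size. If they are dropped, bias is near zero only when loss is unrelated to visit rate. The lost fractions, uniform exit times and within-patient correlation are assumptions.

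Univariate screening with an R² criterion is a stated method that does not serve its stated purpose in a within-patient contrast.

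Two further inferences would go too far. The open choice of test is a small matter, worth about one to two points of type I error. Overdispersion does not invalidate the paired t-test; the case for a rate model rests on time at risk.

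**What to change.** - Name one primary analysis on the rate scale. For example: ED visits by period in a negative binomial or log-link GEE model, with log(days alive and under record coverage) as offset, robust standard errors and a small-sample correction, reporting the rate ratio with 95% CI. Use the same scale in the outcome definition.
- Keep the Wilcoxon test as a sensitivity analysis.
- Replace univariate screening and the R² criterion with pre-specified terms for calendar period and site. Every patient's after-year follows the before-year, so the calendar term relies on comparing patients who start in different years, and the text should say so.
- Add a sensitivity analysis that removes institutional or incarcerated days from the time at risk. The main offset alone corrects only for death and lost coverage.

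**Cost.** Wording, modest programming, and dates of death and institutional stays. Power should not suffer materially: in simulation at n = 29 with a 40% reduction, power was 0.87–0.95 for the t-test and 0.88–0.96 for a log-ratio GEE. The GEE's null rejection was 4.6% to 6.8%, hence the small-sample correction.

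**What it does not fix.** Sites recruit the most frequent users first. Regression to the mean from that selection is untouched by the offset and needs separate treatment.

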### Participants

#### Inclusion criteria

Patients at the study site meeting the following criteria are eligible for participation: aged 21 years or older, have recorded a minimum of two alcohol-related and five all-cause visits to an ED in the preceding 12 months, and are fluent in either English or Mandarin. Patients who discontinued ACT but have completed a minimum of three ACT visits are included, considering that significant interventions would have been implemented into their social, drinking, and medical conditions by the third visit.

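### The intention-to-treat analysis is run only if an undefined complete-set analysis first shows efficacy; it should be unconditional and primary

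*Protocol article*

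**What the plan says.** All references are to the protocol article.

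- **Statistical methods** sets the main comparison: "Using complete set data analysis, cases undergoing ACT will be compared their own historical outcomes as controls". For the primary outcome, "ED utilizations will be compared using the paired sample t-test or Wilcoxon Signed Rank test", with this criterion: "Statistical significance will be set at P < 0.05 criteria". Sidedness is not stated.
- The same section then makes the second analysis conditional: "Should complete set analysis show efficacy, we will proceed to analyze the data using an intention-to-treat analysis". It also says "We will adopt imputation to address missing data", without naming the variables or the analysis set.
- **Inclusion criteria**: "Patients who discontinued ACT but have completed a minimum of three ACT visits are included". The reason given is that meaningful intervention will have taken place by the third visit.
- **The multidisciplinary team-based ACT intervention**: "Patients who opt out of the intervention will still be considered in the analysis".
- **Screening and recruitment** says that relevant outcome data continue to be collected when a participant discontinues or deviates.
- **Primary outcome**: ED visits are "sourced primarily from the electronic records system of the participating hospitals", over 12 months before and 12 months after.
- The **Abstract** and the **Discussion** both anticipate high attrition. The sample size section plans for 15%.

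No section defines the complete set, and none makes the intention-to-treat analysis unconditional or primary.

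**The concern.** An analysis that is run only when another one is positive is reported according to its result. After a null complete-set result, readers would never see the estimate for everyone who enrolled. After a positive one, they would see two estimates with no rule for a disagreement.

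The analysis that decides whether the other is run may also be the more selected of the two. If the complete set follows the three-visit rule, membership depends on behaviour after enrolment. The Background says that these patients often default from addiction treatment, particularly in the first three months, so early leavers could be numerous.

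The primary efficacy claim is at stake, and so is the cost analysis, which takes its savings from the fall in ED encounters. The condition also saves little work: ED counts come mainly from hospital records, and follow-up is meant to continue after discontinuation.

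**Working it through.** **1. The plan's own figure.** Inputs from the sample size section: mean 30.15 visits/year, 40% decrease, SD 23, 80% power, alpha 0.05.

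- Reduction: 0.40 × 30.15 = 12.06 visits.
- Paired normal approximation, two-sided: n = (23 × (1.960 + 0.842) / 12.06)² = 28.55, so 29, as stated.
- Attrition: 28.55 / 0.85 = 33.6, so 34, as stated.

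The 29 is therefore the number expected to remain after 15% attrition.

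**2. Who is analysed.**

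| Section | Patient who leaves before the third ACT visit |
|---|---|
| Inclusion criteria | not among the discontinuers who are kept |
| The multidisciplinary team-based ACT intervention | kept, if an opt-out |
| Screening and recruitment | outcome data still collected |
| Statistical methods, complete set | not determinable |
| Statistical methods, ITT | kept, but only if that analysis is run |

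These statements cannot all be applied without a definition of the complete set.

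**3. Dilution scenario.** Assumptions: drop-outs are outside the complete set and have no change; retained patients fall by 40%; a share f drops out. The all-enrolled reduction is then 40% × (1 − f).

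| f | Complete set | All enrolled | Visits |
|---|---|---|---|
| 0.15 (plan) | 40% | 34% | 12.06 × 0.85 = 10.25 |
| 0.30 (assumed) | 40% | 28% | 12.06 × 0.70 = 8.44 |
| 0.50 (assumed) | 40% | 20% | 12.06 × 0.50 = 6.03 |

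This shows how far the two estimates could differ. It does not measure the harm from the condition itself.

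**4. How often the all-enrolled estimate would be withheld.** Under the same assumptions, the chance that the ITT analysis is not run is 1 − power of the complete-set test (paired t, two-sided 0.05, SD of change 23).

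| f | 34 enrolled: n retained, chance not run | 93 enrolled: n retained, chance not run |
|---|---|---|
| 0.15 | 29, 1 − 0.778 = 22% | 79, 1 − 0.996 = 0.4% |
| 0.30 | 24, 1 − 0.692 = 31% | 65, 1 − 0.986 = 1.4% |
| 0.50 | 17, 1 − 0.528 = 47% | 46, 1 − 0.936 = 6.4% |

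The 93 is the number recruited by March 2023 (Preliminary results). At that size and with the planned effect, the estimate would seldom be withheld. With a smaller true effect it would be withheld more often.

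**5. Selection with no true change.** A simulation (40,000 runs, 34 enrolled, mean change 0, SD 23) made dropout likelier in patients doing worse. Both the direction and the strength of that link are assumptions. The table gives the chance that each test wrongly shows a reduction, against a nominal 2.5% in that direction.

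| Dropout | Complete set: unrelated dropout | Complete set: latent correlation 0.45 | Complete set: latent correlation 0.71 | All 34 |
|---|---|---|---|---|
| 15% | 2.5% | 9.5% | 19.3% | 2.6% |
| 30% | 2.5% | 19.0% | 44.7% | 2.4–2.6% |
| 50% | 2.6% | 30.9% | 71.2% | 2.3–2.6% |

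If dropout is unrelated to outcome, the complete set is not distorted.

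**The case against.** The strongest reply is that the complete set is never defined and never labelled primary. It might simply mean patients with complete ED records. Because those records do not depend on attending ACT, most drop-outs would then be in it, and the gap between 40% and 34%, 28% or 20% would shrink or vanish. This stands: the figures are a scenario, not an estimate of bias in this trial. A condensed article may also leave set definitions to a fuller document. It does not excuse the conditional sentence, which the article itself fixes.

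A reader might draw four stronger conclusions that the document does not support:

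- **Only patients who stayed are analysed.** Discontinuers with three or more visits may be included.
- **Retained patients do better for reasons unrelated to ACT.** The Discussion describes contact lost because ACT led to appropriate institutional care. Such losses need not be failures, so the bias could run either way.
- **Imputation contradicts a complete-set analysis.** It could serve the scale scores, the covariates or the ITT analysis. The Discussion links expected missing data to poor concentration and intoxication, which points to interview data. Only its scope is unstated.
- **ITT after a positive result merely confirms it.** It could also disagree. The gap is that no rule says which result then prevails.

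Records will not capture everything either. They come mainly from participating hospitals, and some patients may be incarcerated or in institutions. That calls for a rule on incomplete counts and does not justify making the analysis conditional.

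**Conclusion.** The point holds in limited form. It is certain from the text that ITT is conditional on a positive result, that the complete set is undefined, that no rule settles a disagreement, and that the sections on discontinuers do not fit together.

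It is possible but not shown that the complete-set estimate is biased by selection after enrolment. The size depends on who is excluded, how many drop out, and how dropout relates to outcome. The document gives only the planned 15% and a warning that attrition may be high. Under the scenario above, a 40% complete-set reduction corresponds to 34% among all enrolled at 15% dropout, and to 28% or 20% at the assumed 30% or 50%. No change in drop-outs may be pessimistic: recruitment favours the most frequent ED users, so some fall through regression to the mean is plausible without ACT.

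The defect matters because it decides which patients support the primary claim. Correcting it removes selection through attrition. It does not remove regression to the mean or time trends, which this single-group design leaves in place.

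**What to change.** 1. Delete the conditional sentence in Statistical methods.
2. State that the primary analysis includes all consented and enrolled patients, whatever number of ACT visits they attended, uses ED counts from records, and is always performed and reported.
3. Define the complete set and label its analysis supportive.
4. State how incomplete 12-month ED counts are handled, for example after death, incarceration or institutional care, and which variables are imputed. Limiting imputation to the scale scores would leave incomplete ED counts without a rule.
5. Reconcile the three-visit rule in the Inclusion criteria with the statements on opt-outs, on continued outcome collection and on the analysis sets.

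The cost is mainly wording, because records data and continued collection are already planned. The headline estimate may be smaller. In the scenario with 34 enrolled and 15% dropout, power is 71% for all enrolled against 78% for the complete set; with 93 enrolled, the all-enrolled analysis has about 99%.
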